### Trial design

After completing the baseline survey on tobacco use, physical health, and mental health, we will use a two-arm study design to randomize 60 patients to counseling + NRT (standard care) or counseling + EC. Participants will receive four counseling sessions in 12 weeks; each session will follow a study visit monitoring any physical or mental changes and side effects from using NRT or EC. All participants will complete a follow-up survey at 24 weeks (Fig. 1). During the 12 weeks of study participation, participants will report their tobacco use daily by responding to automated text messages serving as a smoking diary. We will also invite 20 participants for an in-depth interview on their study experience, outcome expectations, EC perceptions, and barriers to smoking cessation.

**Fig. 1 Fig1:**
[figure not shown]
SPIRIT flow diagram: schedule of enrolment, interventions and assessments

#### Outcomes

Our primary outcomes include: (1) feasibility of intervention, and (2) acceptability of intervention. Secondary outcomes include: (1) change in number of self-reported CC per day based on daily reports that are provided for 84 days post-baseline and (2) change in pulmonary symptoms based on CAT scores at 12 weeks.

#### Randomization

After eligibility screening, participants will be randomized into one of the two study arms (EC or NRT; ratio 1:1) using minimization methodology. This approach has been found to achieve significantly better covariate balance than other randomization methods with a small sample size [30]. Randomization will be stratified by three key variables CAT score (10–19 and ≥ 20), CPD (< 20 and ≥ 20), and sex and will occur using a REDCap based system which includes verification of eligibility criteria prior to the assignment of a study ID and intervention group. Due to the nature of the study, participants are not blind to their randomization allocation.

#### Intervention

##### Intervention arm: EC + counseling

At baseline, intervention arm participants will be provided with a kit containing approximately one month’s supply of EC. If the initial supply does not cover the full month’s use, participants will be able to request an additional supply or change of flavors. A new supply of EC will be distributed regularly during each study visit and as needed for 12 weeks. Participants will be asked to provide regular text messaging check-in reports 4 times over the course of each day to report CC and EC use.

###### Electronic cigarettes

We will use the NJOY “Daily”, an electronic nicotine delivery system that heats an e­liquid to yield an inhalable aerosol. It is manufactured by NJOY LLC, the only major EC company not owned wholly or in part by a tobacco company. NJOY also manufactures the NIDA Standardized Research E-Cigarette [31]. The product is a daily use (approx. 350 puffs) disposable EC with 4.5% nicotine by weight intended to be discarded after its e­liquid has been depleted. One NJOY Daily has the same nicotine content as 1.5 packs of CC. The NJOY Daily is a factory-sealed closed system, which prevents tampering with its designated e-liquid. It is available in two flavors (tobacco and menthol). Participants can choose between tobacco flavor, menthol flavor, or both based on their preference. EC products are all regulated as consumer tobacco products by FDA’s Center for Tobacco Products (CTP). This study examines EC as a harm-reduction strategy, not a smoking cession device. Therefore, the FDA does not require an investigational device exemption (IDE).

##### Control arm: NRT + counseling

Participants in the control arm will be provided with a kit containing a month’s supply of NRT. If the initial supply does not cover the full month’s use, participants will be able to request an additional supply. A new supply of NRT distributed regularly and as needed for 12 weeks. Participants will be asked to provide regular, and very brief, text message check-in reports over the course of each day to report CC and NRT use.

###### Nicotine replacement therapy

Participants with CPD ≥ 10 will be given 21 mg nicotine patches and those with CPD < 10 will be given 14 mg or 7 mg nicotine patches. All participants in this group will also be given 4 mg nicotine lozenges. We will provide sufficient NRT products to participants for 12 weeks.

##### Behavioral counseling

At baseline, all participants will receive a 30-min counseling session delivered by telephone from a counselor trained in motivational interviewing and smoking cessation treatment tailored to the participant’s designated EC or NRT arm. The proposed counseling program has been shown to be acceptable and effective for achieving abstinence in a previous smoking cessation program [57]. Counseling sessions will be similar between the two arms and use the same counseling techniques. Counseling will be provided by a licensed mental health counselor with extensive experience in the field of health psychology and behavioral health research. The same counselor will contact each participant by telephone at 2 weeks and 1 and 2 months to deliver additional 10–15 min counseling sessions, for a total of 4 counseling sessions. For this pilot, a single counselor is expected to complete sessions for all participants, however if additional counselors are used they will be trained to ensure consistent intervention delivery and will evenly split participants between arms.

The purpose of the counseling is to: (1) discuss the impact of continued smoking on their COPD; (2) deliver motivational enhancement for switching from CC to EC (EC arm) or smoking cessation (NRT arm); (3) promote self-efficacy; and (4) inform participants about EC and NRT use. The counseling protocol will be characterized by (1) Motivational enhancement – We will include motivational enhancement in the initial counseling and each of the telephone calls to increase patient motivation to switch from CC to EC or quit smoking; (2) Problem-solving therapy—this approach—endorsed by the national smoking cessation guidelines [32]—will be adapted to focus on helping the smoker identify and solve challenges in switching from CC to EC or quitting smoking.

The counselor will review each participant’s smoking patterns and offer tailored behavioral and environmental change strategies, including specific options such as substituting EC for CC at work, in the home, or least favorite or most favorite CC of the day. Participants will be encouraged to carry their EC at all times for use when avoiding smoking triggers, for use as oral or manual replacement, and provided with other strategies to manage urges. Since there is inadequate evidence that any one of these strategies was more effective than another, participants will be encouraged to choose those that are most appealing. Goal setting and barrier identification will be used to help participants improve confidence in their ability to completely switch to exclusive EC use. Participants will also be provided with information regarding the health risks associated with smoking and advice on smoking cessation will be freely available to all participants at all visits.

Since choosing to use treatment and ultimately to quit is affected by personal, social (e.g., social support) and cognitive (e.g., self-efficacy) factors, counseling will be guided by the framework of Social Cognitive Theory (SCT). SCT has been useful as a theoretical model for understanding barriers and facilitators predicting CC harm reduction [34], particularly with vulnerable groups [35, 36]. Data collected in the in-depth interviews will enable us to refine our counseling content to address factors that may influence CC harm reduction among COPD CC smokers, including social environmental influences, self-efficacy, and outcome expectations [33], as well as other issues specific to specific to COPD.

#### Study visits

Participants will complete study visits by telephone at baseline, 2-, 4-, 6-, 8-, 12- and 24-weeks. At each visit, research assistants will complete a checklist for all activities including completing surveys, assessing for potential harm, monitoring use of non-study supplied nicotine containing products, and confirming adequate supply of EC/NRT.

##### Participation incentives

Participants will have the potential to receive a total of $120 for participating in the study. Participants will not be compensated for study visits or counseling sessions. However, coinciding with study visits, participants will receive $10 for completion of a survey at baseline, 6-, 8-, and 12-weeks, and $20 for completion of a survey at 24-weeks. Additionally, participants can receive up to $40 for completing their daily smoking diaries via text messages ($20 if at least 60% of assessments are completed, $40 if at least 80% are completed). Finally, participants who complete an in-depth interview will receive $20.

##### Data collection and measures

Measures will be collected via survey at baseline and at 6-, 8-, 12-, and 24-weeks, and on a daily basis via the ecological momentary assessment (EMA) text messaging program through week 12. At baseline, all subjects will be surveyed to assess demographics, social support [37], smoking history and habits, smoking cessation self-efficacy [38], tobacco dependence [39], and the treatment offered and used in the prior 12 months, as well as their attitudes toward EC and types of smoking cessation treatment (medications, counseling, and texting). To maximize compatibility with other data and increase the potential for combination with other samples, when possible measures are drawn from NIH initiatives for measure standardization, including the PhenX Toolkit [40], the NIH Toolbox [41], and the Patient Reported Outcomes Measurement Information Systems Initiative (PROMIS) [42]. Relevant tobacco-related measures are drawn from the Population Assessment of Tobacco and Health (PATH) study [43]. Measures not included in the NIH initiatives, such as COPD severity (CAT score), past treatment, and general medical history were derived from the literature. All data will be managed in RedCap.

##### Feasibility and acceptability

The feasibility and acceptability of an EC harm-reduction intervention for patients with COPD who smoke will be assessed with five measures: (1) eligibility and acceptance rate (number accepting enrolment/number eligible); (2) proportion of participants engaging in follow-up visits; (3) retention rate at the end of 12-week treatment period and 24-week follow-up (retained/n); (4) dose of intervention received (e.g., number of counseling sessions); and (5) acceptability of the intervention (satisfaction with EC/NRT) as measured on a 5-point Likert scale. EMA response rate will also be measured.

##### Tobacco product use

CC and EC/NRT product use will be measured as part of a text messaging EMA protocol serving as a smoking diary that incorporates a behavioral “coverage” strategy, designed to maximize the odds that all behavioral events of interest are documented accurately and minimize missing data [44]. Daily recording of product use via EMA allows for measurement of dual use of products and observation of switching patterns. This also provides a measure of CPD over time. After the baseline assessment, participants will be asked to record daily nicotine use by responding to text message prompts. The coverage design prompts participants to provide regular, and very brief, check-in reports via text message over the course of each day, wherein they are asked to report use of EC or NRT based on their study arm and CC over the window of time elapsed since their last report (~ 4 h). One item measures of CC craving and EC/CC satisfaction are collected at each report.

Combined in succession, these coverage reports produce near-complete and consistent use reports over relatively extended periods, partly because they require only seconds for subjects to complete. Text message smoking diary prompts will be automated using SlickText Workflows software and their associated text distribution platform. Frequency of text message prompts will be four per day, corresponding to time windows breaking the day into “Early/Lunch/Afternoon/Evening” periods. There is minimal burden since each data collection instance takes an average of one minute to complete each session. Participants will receive a text message prompt asking them to complete an assessment (Fig. 2). The system is programmed to prevent skipping items or entering out-of-range values. Data is continuously synchronized with a secure web-based HIPAA compliant server. All entries will be time- and date-stamped. The system will record the time it took the participant to respond (response delay), time to completion, and missed prompts. All participants will be instructed how to document their daily tobacco use.

**Fig. 2 Fig2:**
[figure not shown]
Daily text message script

##### COPD symptoms

COPD symptoms, including dyspnea and functional status, will be measured by self-report using three tools including: mMRC (Modified Medical Research Council) Dyspnea Scale examining breathlessness walking [45], COPD Assessment Tool (CAT) score measuring symptoms such as coughing chest tightness, and energy levels [27], and the Clinical COPD Questionnaire (CCQ) measures health status and can be used to assess health-related quality of life [46].

#### In-depth interviews

We will conduct in-depth interviews lasting approximately 30 min with 10 participants in each arm (n = 20) after study visit six (12 weeks post-baseline). Participants will be selected as a convenience sample. At the time of the 6th study visit participants will be invited to participate in an in-depth interview, which will be scheduled and performed via telephone. Recruitment will continue until an n = 10 for each arm is achieved. Excluding specific treatment product satisfaction (i.e. NRT vs EC) prompts, interview questions will be identical for both arms. These assessments will help to gain a more in depth understanding of the participant’s experience, intervention satisfaction, attitudes towards EC, and intentions to quit. These interviews will provide additional insights about the barriers and facilitators of EC use among people with COPD, and how we may refine our approach to enhance retention and outcomes. The interviews will supplement the quantitative data to provide a more in-depth understanding of the feasibility and acceptability of the intervention. Interviews will cover topics such as aspects they like/dislike; features of the intervention that should be modified; their experiences using EC/NRT; intentions of using EC after the intervention (NRT regimen is typically 2–3 months); and whether their COPD symptoms interfered with their ability to engage in the intervention. The interviews will also be used to further adapt the behavioral counseling manual to an EC intervention for a future trial. The interviews will be audio recorded and participants will be required to provide audio consent prior to conducting the interview. Recordings will be transcribed with personal identifiers removed, and the actual recording will be destroyed at the end of the study.

#### Statistical methods

Before addressing the study aims, data will be summarized numerically using descriptive statistics. Comparison of the baseline characteristics between the study arms will be performed using chi-square tests for categorical data and t-tests or nonparametric tests for ordinal or continuous data. Preliminary analyses will investigate possible differences on the primary outcomes by gender and race/ethnicity. If differences appear, race/ethnicity and/or gender will be entered as covariates. Exploratory analyses will be conducted where appropriate to better understand the findings. Otherwise, analyses will collapse across race/ethnicity and gender. All data will be presented in aggregate and de-identified prior to publication.

Feasibility and acceptability will be summarized using descriptive statistics. Simple logistic regressions, including ordinal and multinomial models, will be used to compare the characteristics of participants reporting high and low acceptability. We will evaluate the impact of EC vs. NRT on the reduction in self-reported CPD and CAT Score, at 12 and 24 week follow-up assessments, with and without the addition of covariates. CPD at baseline and 12 weeks will be extracted from EMA data, while the 24-week follow-up will be self-report from the telephone survey. The impact of EC vs. NRT on change in CPD and CAT Score will be estimated using a Poisson or negative binomial regression model [47] with follow-up CPD/CAT Score regressed on baseline CPD/CAT Score and an indicator variable of study condition (EC vs. NRT).

This study is not meant to provide a definitive test of intervention efficacy and will be used to inform future sample sizes for a larger trial [48, 49]. In the primary analysis the sample size is anticipated to provide 80% power to detect a difference of 0.73 points in intervention satisfaction between study arms. For other primary measures, the sample size is anticipated to provide exploratory results to examine observed trends, but not statistically significant difference. For secondary analyses of effectiveness, in a Poisson generalized linear model for the number of CC reduced from baseline to follow-up, we will have greater than 90% power to detect a rate ratio of RR = 1.60 (e.g., a reduction by 5 CC per day in the NRT condition vs. 8 in the EC condition). If there is marked overdispersion of the number of CC per day reduced (κ = 0.2), we will still have greater than 80% power to detect RR = 1.80 (e.g., 5 vs. 9 CC per day reduction). Similarly, without considering covariates, we have 80% power to detect a difference of at least 2.7 on the CAT score, and with effective covariates, we have 80% power to detect a difference of 2.2. Translated to standardized mean differences, these are modest effects (d = 0.33 and d = 0.26). In secondary analyses, we will consider CPD collected daily over a 14-day period prior to the end of the 12-week follow-up. This will increase the power by increasing sample size providing for greater than 90% power to detect a rate ratio of RR = 1.20 (e.g., a reduction by 5 CC per day in the NRT condition vs. 6 in the EC condition). If there is marked overdispersion of the number of CC per day reduced (κ = 0.2), we will still have greater than 80% power to detect RR = 1.40 (e.g., 5 vs. 7 CC per day reduction).

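### Neither effect model prespecifies all three minimisation factors, and adjustment for sex depends on an undefined screen of other outcomes

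*Protocol article*

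**What the plan says.** **Allocation.** The Randomization section assigns patients "ratio 1:1) using minimization methodology". It continues "Randomization will be stratified by three key variables CAT score" and names CAT score (10–19 or ≥ 20), CPD (< 20 or ≥ 20) and sex. Sixty patients are randomised.

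**Effect models.** Statistical methods estimates the effect on CPD and CAT by Poisson or negative binomial regression, "with follow-up CPD/CAT Score regressed on baseline CPD/CAT Score and an indicator variable of study condition". The effects are to be evaluated both with and without covariates. Those covariates are not listed, and neither version is named as the main one.

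**Gender and race/ethnicity.** The same section says "Preliminary analyses will investigate possible differences on the primary outcomes by gender and race/ethnicity". It then says "If differences appear, race/ethnicity and/or gender will be entered as covariates", and for the other case "Otherwise, analyses will collapse across race/ethnicity and gender".

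**Which outcomes are primary.** The Outcomes section lists feasibility and acceptability as primary. Change in CPD and change in CAT are secondary.

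**The concern.** Minimisation removes much of the chance imbalance between arms on its factors. The standard error reflects that gain only if the analysis model contains those factors. When a prognostic factor is balanced by design but absent from the model, its variance stays in the error term. The reported standard error is then larger than the true sampling variation of the effect estimate.

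The gender rule adds a second difficulty. Sex was judged important enough to allocate by, yet its default treatment in the analysis is to be collapsed over. It returns only after a look at the data. That look has no test or threshold, is made on outcomes other than CPD and CAT, and is not tied to any particular model. With adjusted and unadjusted versions both planned and neither ranked, the main estimate is undefined.

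At stake is precision in a 60-patient trial. Statistical methods also says the results will inform the size of a larger trial.

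**Working it through.** **1. Which factors each model names**

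| Minimisation factor | CPD model | CAT model |
|---|---|---|
| CPD | yes, as own baseline | not named |
| CAT | not named | yes, as own baseline |
| Sex | only if a difference is seen | only if a difference is seen |

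Each model is sure of one factor out of three.

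**2. The plan's own figure on covariates.** Statistical methods gives a detectable CAT difference of 2.7 points without covariates and 2.2 with them. The implied share of variance explained is 1 − (2.2/2.7)² = 0.34. The plan therefore counts on adjustment, but does not say which variables provide it.

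**3. Cost of omission, by formula.** Let R² be the share of residual variance explained by the omitted factors. The documents give no value, so 0.10 and 0.20 are assumptions. For a linear model with the factors well balanced:

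- Standard error ratio, 1/√(1 − R²): 1/√0.90 = 1.054 and 1/√0.80 = 1.118, so about 5% and 12% too wide.
- True two-sided type I error, P(|Z| > 1.96/√(1 − R²)): P(|Z| > 2.07) = 0.039 and P(|Z| > 2.19) = 0.028.
- If the residual variance were used to size a later trial that does adjust, that trial would be too large by 1/(1 − R²): 1.11 and 1.25.

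**4. Cost of omission, by simulation.** The setting was 60 patients, biased-coin minimisation (probability 0.8) on the three factors, a linear CAT-like outcome with residual SD 4, and 4,000 runs per scenario. The prognostic strengths are assumptions.

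| Effect of sex and of CPD ≥ 20 (points each) | Type I error, own baseline only | Type I error, CAT + CPD + sex | Power for 3 points, own baseline only | Power for 3 points, CAT + CPD + sex |
|---|---|---|---|---|
| 0 | 0.053 | 0.049 | 0.83 | 0.82 |
| 2 | 0.038 | 0.050 | 0.77 | 0.80 |
| 4 | 0.018 | 0.047 | 0.67 | 0.78 |

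**5. Does the screen create false positives?** The worst case was simulated, with sex and race/ethnicity screened at p < 0.05 on the analysed outcome itself. Type I error was 0.052, 0.040 and 0.030 in the three scenarios. With no true gender or race/ethnicity effect, the screen still picked a covariate in about 10% of trials (two independent looks: 1 − 0.95² = 0.0975). Taking the smaller p-value of the runs with and without covariates raised type I error from 0.053 to 0.059 in the no-effect scenario.

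**6. Which CPD value could be used.** Statistical methods takes baseline CPD from the text-message diary. The Tobacco product use section starts that diary after the baseline assessment and asks about EC or NRT according to arm. The diary value may therefore be recorded after allocation and be affected by treatment. The CPD value used for minimisation is fixed before allocation.

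**The case against.** A reader might infer that the analysis ignores the allocation scheme, or that the minimisation factors are simply left out. The text does not support that. Each model carries the baseline of its own outcome, which is itself a minimisation factor and often the strongest predictor. Sex may enter conditionally, and the unlisted covariates could include the rest. A full covariate list is also something a condensed article may leave to the analysis plan.

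A reader might also infer that CPD or CAT results drive the choice of covariates and so inflate the error rate. The text does not say that either. The screen is on feasibility and acceptability and compares gender and race/ethnicity groups, not arms. Whether it carries over to the CPD and CAT models is unclear. Even screening on the analysed outcome produced no material inflation.

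Reporting results with and without covariates is not a fault in itself; only the ranking of the two is missing. The 10% and 20% figures have no source in the documents, and the calculation is linear while the planned models are Poisson or negative binomial. The effect aims are stated to be exploratory.

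These objections limit the size of the point but do not remove it. The conditional rule for gender is a written instruction, not an omission that a later document would merely fill in. By default it drops a variable that the trial allocates by.

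**Conclusion.** The point holds as a moderate one about precision and clarity. Neither effect model is stated to include all three minimisation factors, and adjustment for sex depends on an unspecified reading of other outcomes.

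The size depends on how prognostic the unnamed factors are. In the simulation the loss of power ran from nil, through about 3 points when sex and CPD are worth 2 CAT points each, to about 11 points at 4 each. The corresponding type I errors were 0.053, 0.038 and 0.018, so where there is an error it is conservative. These sizes rest on a linear model and assumed prognostic strengths, and need not carry over exactly to the planned count models. The documents do not support a charge of inflated false positives.

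**What to change.** - Delete the two sentences that enter gender and race/ethnicity if differences are seen and otherwise collapse over them.
- State that all CPD and CAT models include arm, baseline CAT, sex and the pre-randomisation CPD value used for minimisation. Say explicitly that this is not a diary value collected after allocation. In the CPD model it takes the place of the diary-derived baseline.
- Name this adjusted estimate as the main reported result. Make the unadjusted and race/ethnicity-adjusted results sensitivity analyses.

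The cost is a few sentences and about two degrees of freedom per model in an exploratory analysis. No new data are needed, because all three variables are already required for allocation. In the simulation, when the added factors were not prognostic, power was 0.82 instead of 0.83.

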Our study protocol has a few limitations. First, as a pilot study the protocol is not powered to detect small differences in CPD or CAT Scores between the NRT and EC arms. Second, CAT Score is not the gold standard for the assessment of respiratory health. If this study is successful, future research needs to include assessment of airflow by spirometry, as well as by assessment of small airway function using respiratory oscillometry. While FEV1 change is not typically observable in early stage COPD patients, oscillometry may identify the presence of small airway injury in this population [72]. Adherence to study medications is not directly measured, therefore analyses are limited to intent-to-treat rather than per-protocol. The NJOY EC used in the study is not representative of all EC available and additional research using alternate products is called for. EC contain nicotine, which is an addictive substance and therefore there is potential for participants to continue EC use after the study is complete. The counseling protocol does not include EC cessation. Future research on EC cessation methods and continued EC use after switching is called for. Finally, all study measures are self-report. Future studies should include bio-confirmation of CC reduction such as CO.

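### Week-12 cigarettes per day is taken only from the text diary, so a participant who has stopped texting has no observed week-12 value even when reached at the scheduled 12-week telephone visit

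*Protocol article*

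**What the plan says.** In the protocol article, Statistical methods assigns the CPD sources by time point: "CPD at baseline and 12 weeks will be extracted from EMA data", and CPD at week 24 comes from the telephone survey. Outcomes agrees, listing as the first secondary outcome "change in number of self-reported CC per day based on daily reports that are provided for 84 days post-baseline".

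Contact at week 12 does not depend on the diary. Study visits says "Participants will complete study visits by telephone at baseline, 2-, 4-, 6-, 8-, 12- and 24-weeks", and Data collection and measures says "Measures will be collected via survey at baseline and at 6-, 8-, 12-, and 24-weeks". Neither section makes the 12-week call or survey a source of week-12 CPD, and the article does not say whether that survey asks about CPD.

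The stated model regresses follow-up CPD on baseline CPD and study arm. The limitations paragraph of the Discussion says that adherence is not directly measured, "therefore analyses are limited to intent-to-treat rather than per-protocol".

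**The concern.** The model needs a follow-up CPD for each participant. Under the stated source rule, someone who has stopped answering texts by the end of treatment has none, although a research assistant may be speaking to that person at week 12. The same person could be scored by telephone at week 24.

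The trial is open-label, and answering four texts a day for 84 days (336 prompts) takes persistence. It is plausible, though the article does not say so, that those who go silent are smoking more or like their assigned product less. The week-12 estimate would then describe continuing texters. Within each arm the reduction would look better than it is. Between arms, a difference could be created or hidden if silence is unequal. Estimating the 12-week reduction in CPD is the study's second aim, and the results are meant to inform the size of a larger trial, so a selective estimate would be carried forward.

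**Working it through.** **Is this a stated rule or only a gap?** Statistical methods names one source for week 12 and a different one for week 24, and Outcomes defines the measure from the daily reports. The source is therefore fixed in the text. How missing values are then handled is not stated.

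**Does the diary design prevent the problem?** Tobacco product use describes a coverage design meant to limit missing data, and Participation incentives pays at 60% and 80% completion. Overall completion does not determine what is available at the end. The only closing window the article names is the 14 days before the end of week 12, used for a further secondary analysis.
- That window holds 14 × 4 = 56 prompts. Answering 60% of prompts evenly gives 0.60 × 56 ≈ 34 reports there, which is ample.
- Answering every prompt for 70 days and none afterwards gives 70/84 = 83% completion, above the upper payment tier, and no report in the window.

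So the tiers neither forecast silence at week 12 nor protect against it.

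**The plan's own power figures.** Statistical methods claims more than 90% power for a rate ratio of 1.60 (reductions of 5 v 8) and more than 80% for 1.80 (5 v 9) with overdispersion κ = 0.2. I assume n = 30 per arm, two-sided α = 0.05 (the article gives no α) and a Wald test on the log rate ratio:

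power = Φ( ln RR / √[(1/m₁ + κ)/n + (1/m₂ + κ)/n] − 1.96 )

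- RR 1.60, κ = 0: 0.470/√(0.325/30) − 1.96 = 2.56, power 99.5%.
- RR 1.80, κ = 0.2: 0.588/√(0.711/30) − 1.96 = 1.86, power 96.8%.

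Both claims hold with all 60 scored. With 40% unscored (18 per arm) the values are 93.8% and 84.1%, so both still hold. With 50% unscored (15 per arm) they are 89.1% and 77.0%, and both fail. Lost power is therefore not the main issue; selection is.

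**Size of the selection effect, under assumptions.** Suppose there is no true arm difference and true mean CPD is 10, with half the participants at 14 and half at 6. Only the heavier half goes silent. If a share s of an arm is silent, the observed mean is (10 − 14s)/(1 − s).

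| Silent, NRT v EC | Observed mean, NRT | Observed mean, EC | False difference |
|---|---|---|---|
| 20% v 20% | 7.2/0.8 = 9.00 | 9.00 | 0 |
| 30% v 10% | 5.8/0.7 = 8.29 | 8.6/0.9 = 9.56 | 1.27 |
| 40% v 20% | 4.4/0.6 = 7.33 | 7.2/0.8 = 9.00 | 1.67 |

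In the two unequal rows the error runs against EC; reversing the silence reverses the direction. Simulation of these scenarios (30 per arm, negative binomial counts with κ = 0.2, unadjusted t-test) gives a type I error of about 9–10% and 12–13% in place of 5%.

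The protocol's model adjusts for baseline CPD. In a simulated linear model with an assumed baseline that predicts heaviness (means 20 and 12), the false differences fell to about 0.9 and 1.1 CPD, with type I error of 7.4% and 8.1%. How much adjustment removes depends on how well baseline predicts who goes silent. Silence driven by failure to reduce, independently of baseline, would not be removed.

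**The case against.** The strongest objection is that the article does not say silent participants are dropped. It names a data source and a model and is silent on missing data. Imputation, use of earlier diary days and a minimum number of days are commonly left to an analysis plan, and their absence here is no finding. This stands: complete-case analysis is an inference. What remains is narrower. No later analysis choice can supply a week-12 observation that the stated source rule does not use.

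A reader might infer that such participants cannot be scored at all, or that the plan contradicts its own intent-to-treat statement. Neither is supported. Someone who stops at week 8 has weeks of diary data, and someone who stops late still contributes some closing days. The Discussion uses the phrase intent-to-treat only in contrast to a per-protocol analysis, because adherence is not measured. It does not promise an observed outcome for all 60.

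It is also fair to say that the primary outcomes are feasibility and acceptability, that the effect aims are declared exploratory, and that missed prompts and the EMA response rate are recorded, so diary silence will be visible. That lowers the importance of the point.

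Finally, replacing diary values by recall for silent participants would mix instruments at one time point, and unequally if silence is unequal. This is a good reason to keep the telephone value to a flagged sensitivity analysis. The telephone question also does not recover those who withdraw fully or are withdrawn, for example for pregnancy.

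**Conclusion.** The point holds as a modest improvement. The article takes week-12 CPD, the first-listed secondary outcome, only from the diary, while a telephone contact that could supply it is already scheduled and telephone CPD is accepted at week 24. The week-12 estimate therefore rests on continuing texters.

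The size of any bias is unknown. The illustration of about 1.3 CPD (30% v 10% silent) assumes that silence occurs only among heavier smokers, uses assumed silence rates and is unadjusted. It is smaller when baseline predicts heaviness, and there is no false arm difference when silence is equal. Equal silence would still flatter each arm's level (9.0 in place of 10 at 20% silent).

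**What to change.** - Ask the week-24 CPD question in the existing 12-week telephone survey as well. If it is already asked there, name it as a source of week-12 CPD.
- Keep the diary as the main source, and state how many diary days in the closing window make a usable week-12 value.
- Add a sensitivity analysis that uses the telephone CPD, flagged by source, for participants without usable closing-window diary days.
- Report by arm how many participants are scored from the diary, from the telephone only, and from neither.

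The cost is at most one question at a scheduled call and one extra analysis. The downside is that a minority of values in that sensitivity analysis come from recall and not from the diary. Participants missing from both sources remain missing, and the report by arm will show how many there are.
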